##### 8.3.1.4. Serious Adverse Event (SAE)

An SAE refers to one of the following conditions that occur in a patient after receiving the study drug in a clinical study:

- (1) Leading to death;
- (2) Life-threatening;

The term "life-threatening" in the definition refers to the risk of death for the patient at the time of the event, rather than the possibility of death if the event worsens.

(3) Requires hospitalization or prolongation of hospitalization;

However, the following admissions are not considered SAEs:

- Less than 24 hours in hospital.
- Pre-planned hospitalization (e.g., elective or scheduled surgery arranged prior to the start of the study; hospitalization is part of the study procedure).
- Hospitalization is not related to AEs (such as social hospitalization for short-term care purposes).

(4) Permanent or severe disability or loss of function;

Loss of function refers to a severe impairment of the normal life ability of an individual.

(5) Congenital anomaly or birth defect.

(6) Other medically significant events.

Important medical events may not immediately endanger life, cause death, or require hospitalization, but are generally considered serious if medical intervention is needed to prevent any of the aforementioned outcomes. For example, important treatments in the emergency room, allergic bronchospasm occurring at home, non-hospitalized malnutrition or seizures, drug dependency, or addiction.

#### **8.3.1.5. Suspected Unexpected Serious Adverse Reaction (SUSAR)**

Suspected and unexpected serious adverse reactions with the nature and severity of the clinical presentation out of the range of the information available in the investigator's brochure, package insert of marketed drugs, or product characteristics summary.

#### **8.3.1.6. Adverse Events of Special Interest (AESI)**

Adverse events of special interest (serious or non-serious) are a type of event that is of scientific and medical concern for the sponsor's drug or study project. Such events usually require further investigation to describe their characteristics and gain understanding. Given the nature of these events, continuous monitoring is required, and a rapid communication mechanism should be established between the investigator and the sponsor.

### 8.3.2. Adverse Event Assessment Category

According to the following criteria, the investigator should assess and record all of AEs.

#### 8.3.2.1. Seriousness

For each AE, severity must be determined according to the definition of SAE.

#### 8.3.2.2. Severity

The severity of AEs will be recorded using the Common Terminology Criteria for Adverse Events, which is a standard terminology developed by the National Cancer Institute (NCI-CTCAE, version 5.0). If an AE falls outside the scope of this standard, the investigator will be according to Table 8-2 for assessment.

**Table 8-2 Severity Criteria**

| Grading | Severity Description                                                                                                                                                                                                                                                                                                                   |
|----------------|-----------------------------------------------------------------------------------------------------------------------------------------------------------------------------------------------------------------------------------------------------------------------------------------------------------------------------------------------|
| Grade 1:       | Mild; asymptomatic or mild; only observed clinically or diagnostically; no treatment required.                                                                                                                                                                                                                                                |
| Grade 2:       | Moderate; requires minor, localized, or non-invasive treatment; limited instrumental activities of daily living (IADLs) commensurate with age (IADLs refer to activities such as cooking, shopping for clothes, using the telephone, managing finances, etc.).                                                                                |
| Grade 3:       | Severe or clinically significant but not immediately life-threatening; resulting in hospitalization or prolonged hospital stay; causing disability; limiting self-care activities of daily living (self-care activities of daily living refer to bathing, dressing, eating, grooming, taking medication, etc., and do not include bedridden). |
| Grade 4:       | Life-threatening; urgent treatment indicated.                                                                                                                                                                                                                                                                                                 |
| Grade 5:       | Deaths related to AEs.                                                                                                                                                                                                                                                                                                                        |

### 8.3.3. Causality

#### 8.3.3.1. Causality between Adverse Events and Study Drug

For all AEs, investigators should assess the causal relationship between each event and each study drug separately. The assessment of causality should be performed by an authorized clinical physician, who should not only determine whether there is a causal relationship with the study drug, but also provide as much detail as possible regarding the basis for the determination.

Approach to assessment: Important factors to consider when evaluating the causal relationship between AEs and study drug include:

a. Temporal relationship to dosing

The event should have occurred after the drug administration. The time interval between drug exposure and the occurrence of the event should be evaluated in the clinical context of the event.

b. Reactions after discontinuation (dechallenge) and re-administration (rechallenge) of the medication.

The response of the patients after dechallenge or rechallenge should be evaluated based on the common clinical course of relevant events.

c. Underlying disease, concomitant disease, concurrent disease.

Each event should be evaluated in the context of the current treatment of the disease and the patient's medical history and course of any other underlying conditions.

d. Concomitant Medications or Treatments

The investigator should examine the other drugs or treatments that the patient is receiving when AEs occur, to determine if they may have contributed to the event.

e. Known types of reactions (clinical/preclinical) for such drugs

f. Exposure to physical/psychological stress

Exposure to stress may induce adverse changes in patients and provide a more reasonable explanation for this event.

g. Pharmacology and PK of study treatment

The PK properties of the therapeutic agent (absorption, distribution, metabolism, and excretion), as well as the pharmacodynamics of individual patients, should be taken into account when conducting the investigation.

The relationship between the study drug and AEs is classified as follows: related, probably related, possibly related, possibly unrelated, not related. The specific criteria for determining the relationship are shown in Table 8-3.

**Table 8-3 Determination of the Relationship between Adverse Events and Study Drug**

| Related | Probably related | Possibly related | Possibly unrelated | Not related |
|----------------|-------------------------|-------------------------|---------------------------|--------------------|
|----------------|-------------------------|-------------------------|---------------------------|--------------------|

|                                                                                                                                                    |   |   |    |    |   |
|----------------------------------------------------------------------------------------------------------------------------------------------------|---|---|----|----|---|
| a. Is there a reasonable temporal relationship between the event and the study drug?                                                               | + | + | +  | +  | — |
| b. Does the event match the known adverse reactions of the drug?                                                                                   | + | + | ±  | —  | — |
| c. Does the event resolve or disappear after discontinuation or dose reduction?                                                                    | + | + | ±? | ±? | — |
| d. Does the event reappear after re-dosing?                                                                                                        | + | ? | ?  | ?  | — |
| e. Can the effect of combination therapy, the progression of patients' condition, and the impact of other treatments be used to explain the event? | — | — | ±  | ±  | + |

Note: + indicates positive, - indicates negative, ± indicates uncertain, ? indicates unclear.

When there is incomplete correspondence with a certain evaluation result or uncertainty about whether a clinical observation is an AE, strict evaluation and reporting should be conducted.

### 8.3.3.2. Causality to Study Procedures and Operation

Based on the question of whether there is a “reasonable causal relationship” between AEs and the study protocol, the evaluation results should be recorded as "related" or "not related" in the CRF. Generally refers to AEs caused by harm or injury to any clinical procedures (such as tissue biopsy), AEs caused by drug discontinuation, dose reduction or adjustment of treatment regimen required by the study protocol, or AEs caused by other prophylactic medications administered prior to the study drug.

### 8.3.4. Action Taken with Study Treatment

Record all measures taken to address AEs related to the study drug according to the following categories. Specific measures should be detailed in the CRF.

- Permanently discontinue
- Drug interruption

- Dose reduction
- Dose unchanged
- N/A
- Unknown

### **8.3.5. Other Specific Treatment for Adverse Events**

- No treatment was received
- Drug therapy
- Other treatments

### **8.3.6. Outcome**

The outcome of the AE will be recorded as follows:

- Recovered/resolved
- Recovering/resolving
- Recovered/resolved with sequelae
- Not recovered/not resolved/ongoing
- Fatal
- Unknown

### **8.3.7. Collection, Recording and Evaluation of Adverse Events**

The investigator is responsible for collecting all adverse medical events that occur from the signing of the informed consent form to the end of the safety follow-up period (28 days  $\pm$  3 days after the last dose).

After the end of the safety follow-up period, AE will no longer be actively collected. If an SAE occurs and the investigator believes there is a reasonable causal relationship between the SAE and the study drug, the SAE should be reported to the sponsor according to the SAE reporting process.

AEs that have not fully recovered or stabilized by the end of the safety follow-up period (regardless of causality), follow-up must be conducted until recovery (to baseline or complete recovery), clinical stability is achieved, or a reasonable explanation is obtained.

AEs occurring between the informed consent form and first use of the drug may be recorded in

the CRF as medical history/accompanying diseases unless they meet one of the following criteria, in which they should be recorded as AEs: harm caused by any clinical laboratory examination procedures; AEs caused by discontinuation of the study protocol; AEs caused by drugs other than the study drug.

All AEs that occur during the safety follow-up period after the first administration of the drug must be recorded, including information such as the name, the start and end dates (and times) of the AE, severity, seriousness, the investigator's assessment of the relationship with the study drug, measures taken for the study drug in response to the AE, and outcome.

- If a patient dies, the cause or symptom leading to the death should be reported as the AE name. "Death" should be considered as an outcome of the AE. If the cause of death is unknown, "death of unknown cause" should be reported as the AE name.
- Events that clearly correspond to the progression of the tumor disease should not be recorded as AEs. However, if the investigator determines that the event is atypical, accelerated progression, or caused by the study drug, it should be recorded as an AE.
- Any death event caused by any reason during the safety follow-up period should be reported to the sponsor according to the SAE process.

The investigator is responsible for determining the causal relationship between recorded AEs and the study drug, as well as the study procedures and operations, as outlined in section 8.3.3. The sponsor must conduct a separate assessment of the expectedness, severity, and causal relationship between SAE and the study drug. The reference document for the expectedness assessment is the most current version of the Investigator's Brochure (IB).

### **8.3.8. Reporting of Serious Adverse Events**

#### **8.3.8.1. Investigator Responsibilities**

##### **Reporting Sponsor**

For all SAEs and follow-up information that occur during the observation period described in section 8.3.7, the investigator must report to the sponsor within 24 hours of becoming aware. In the case of reports involving death, the investigator should provide the sponsor with additional information as needed, such as autopsy reports and final medical reports.

### **Reporting Ethics Committee**

The investigator should promptly acknowledge receipt and review of relevant safety information provided by the sponsor regarding the clinical study, and consider whether the treatment of the patients has been adjusted accordingly. If necessary, The investigator should communicate with the patients as early as possible and report any suspected and unexpected serious adverse reactions provided by the sponsor to the ethics committee. In the case of a report involving a death event, the investigator should provide the ethics committee with other necessary information, such as autopsy reports and final medical reports.

#### **8.3.8.2. Responsibilities of the Sponsor**

The sponsor should report suspected and unexpected serious adverse reactions to the drug regulatory authority and the health department promptly. The reporting time limit is as follows:

- For fatal or life-threatening SUSARs, they should be reported within 7 days of first knowledge (day 0 being the day the sponsor first becomes aware) and followed up with additional information within the following 8 days.
- Report non-fatal or non-life-threatening SUSARs within 15 days.
- For follow-up reports, report within 15 days of obtaining new information.

The sponsor should promptly report any suspected and unexpected serious adverse reactions to all investigators and testing facilities, as well as the ethics committee involved in the clinical study.

#### **8.3.8.3. Adverse Events of Special Interest**

For AESIs, investigators should report to the sponsor following the SAE reporting process within 24 hours of becoming aware of the event.

AESIs in this study are:

- Prolongation of QT interval on electrocardiogram (graded as  $\geq 3$  on CTCAE scale).

#### **8.3.9. Pregnancy**

The investigator must report all pregnancy events that occur in female patients during the administration of the drug and throughout the safety follow-up period to the sponsor. Pregnancy outcomes should be carefully monitored and any abnormal outcomes in the mother or infant

should be reported.

If a male patient's partner becomes pregnant, information regarding the pregnancy process and outcome should be obtained with the partner's consent as soon as possible.

Once a pregnancy event occurs during the safety follow-up period after administration, the investigator should communicate with the patient in a scientific and rigorous manner based on the drug information, informing her/him of the potential impact and risks of the study treatment on pregnant women and fetuses. If a female patient experiences a pregnancy event, the investigator should immediately suspend the clinical study for that patient and discontinue the study treatment.

Within 24 hours of confirming a pregnancy event in a patient (or patient's partner), the investigator should complete a pregnancy report form and report to the sponsor (institutional review board, if required).

The investigator will complete a pregnancy report form and submit a follow-up report to the sponsor (and the institutional review board if required) within 24 hours of being informed of the pregnancy outcome.

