|  | 
there is clear disease progression after radiotherapy);
 
7. Eastern Cooperative Oncology Group (ECOG) performance status (PS) score 0-1;
 
8. Adequate organ function, defined as:
 
 
• Neutrophil count (ANC) <math>\geq 1.5 \times 10^9/L</math> (no G-CSF for WBC-elevating therapy within 2 weeks prior to the laboratory test);
 
• Platelet count (PLT) <math>\geq 75 \times 10^9/L</math> (not receiving platelet transfusion or other drugs to promote platelet production within 2 weeks prior to the laboratory test);
 
• Hemoglobin (Hb) <math>\geq 90</math> g/L; (not receiving red blood cell transfusion or erythropoiesis-stimulating drugs within 2 weeks prior to the laboratory test);
 
• Alanine aminotransferase (ALT) and aspartate aminotransferase (AST) <math>\leq 3 \times</math> upper limit of normal (ULN) (<math>\leq 5.0 \times</math> ULN for patients with liver metastases);
 
• Serum total bilirubin (TBIL) <math>\leq 1.5 \times</math> ULN;
 
• Serum creatinine <math>\leq 1.5 \times</math> ULN;
 
• Albumin <math>\geq 30</math> g/L;
 
 
9. Male and female patients of childbearing age agree to take effective contraceptive measures during treatment and within 6 months after the last dose of treatment.
 
Exclusion Criteria
 
1. Have a documented carcinogenic-driver gene alteration other than RET in NSCLC, including activating EGFR, BRAF, or KRAS mutation, MET exon 14 skipping mutation or high-level amplification, and ALK, ROS1, or NTRK1/2/3 gene fusions;
 
2. Prior treatment with selective RET inhibitors (including investigational RET inhibitors, such as LOXO-292, BLU-667, RXDX-105, vandetanib, cabozantinib, etc.);
 
3. Patients who have previously received any anti-tumor therapy within 4 weeks before the first use of the study treatment (including but not limited to chemotherapy, radiotherapy and targeted therapy, etc.); Patients treated with traditional Chinese medicine or Chinese patent medicine with anti-tumor indications or local palliative radiotherapy for the pain relief of bone metastasis should have a two-week period of detoxification;
 
4. Abnormal coagulation function (INR <math>> 1.5</math> or APTT <math>> 1.5 \times</math> ULN), bleeding tendency (such as an active peptic ulcer), or current treatment with
 |

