## 1.2. Schedule of Assessment

| Test Period                                                            | Screening |       | Treatment Period |          |          | End of
Treatment/Withdrawal Visit
(EOT) [3] | Safety Follow-up Period    | Follow-
up     |
|------------------------------------------------------------------------|-----------|-------|------------------|----------|----------|---------------------------------------------------|----------------------------|-------------------|
| Visit time                                                             | -28~-1    | -7~-1 | C1D1             | C1D15[1] | CnD28[2] | Within 14 days of the last
dose                | Day 28 after the last dose | Every 12
weeks |
| Window                                                                 | N/A       | N/A   | N/A              | ± 1 day  | ± 3 days | N/A                                               | ± 3 days                   | ± 7 days          |
| Informed Consent                                                       | ×         |       |                  |          |          |                                                   |                            |                   |
| Demographic data [4]                                                   | ×         |       |                  |          |          |                                                   |                            |                   |
| Height/Weight [5]                                                      | ×         |       |                  |          | ×        | ×                                                 |                            |                   |
| Tumor History and Treatment
History [6]                             | ×         |       |                  |          |          |                                                   |                            |                   |
| Tumor tissue samples or blood
collection [7]                        | ×         |       |                  |          |          |                                                   |                            |                   |
| Personal and other past medical
history or concomitant diseases [8] | ×         |       |                  |          |          |                                                   |                            |                   |

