|  | 
according to the actual situation of the patients.
 
[10] Pregnancy Testing: Women of childbearing age should undergo pregnancy testing (excluding those who have undergone sterilization, oophorectomy and/or hysterectomy), and both blood HCG pregnancy testing and urine HCG pregnancy testing are acceptable. Women in menopause who have not yet reached postmenopausal status (12 consecutive months of amenorrhea) are considered to be capable of reproduction.
 
[11] Twelve-lead electrocardiogram: During the screening period, two 12-lead electrocardiogram tests should be performed within 7 to 1 day(s) before baseline. The average of the QTcF values from the two tests will be used as the baseline. If any of the test results meet the exclusion criteria (11), the patient will not be enrolled in the study.
 
[12] PK Sample Collection: For patients enrolled after the execution date of the revised protocol (V3.0), blood samples for PK analysis should be collected at any time point on C1D1 4-8 hours after dosing, before (-30min) and 4-8 hours after dosing on C1D15 (<math>\pm 1</math> day), and at any time point on C1D28 (<math>\pm 3</math> days), C2D28 (<math>\pm 3</math> days), C4D28 (<math>\pm 3</math> days), and C6D28 (<math>\pm 3</math> days). For patients who are enrolled before this date and have not terminated treatment, blood samples for PK analysis can be collected at any time point during any two visits of C1D15 (<math>\pm 1</math> day), before (-30min), and 4-8 hours after dosing (if applicable), and CnD28 (<math>\pm 3</math> days). 3ml of blood should be collected each time, and the time of dosing and actual sampling time should be recorded. If a patient terminates treatment for any reason during the study period, a blood sample can be collected for PK analysis on the day of the EOT visit as appropriate.
 
[13] Tumor imaging evaluation: Tumor imaging evaluation should be conducted every 8 weeks (<math>\pm 7</math> days) from C1D1 until week 40, and then every 12 weeks (<math>\pm 7</math> days) thereafter, until disease progression, initiation of new anti-tumor therapy, death, or patient withdrawal from the study (whichever occurs first). Patients judged as CR and PR must undergo efficacy confirmation at least 4 weeks later.
 
[14] Concomitant medication/treatment: Collect all concomitant medication/treatment from patients during the 28 days prior to the first drug administration until the safety follow-up period. For drug treatment, record the generic name, single dose, frequency of administration, reason for treatment, start date, and end date. For non-drug treatment, record the treatment name, start and end dates.
 
[15] AEs: Collection of AEs should be conducted from the signing of the informed consent form to the end of the safety follow-up period. If a serious adverse event (SAE) occurs after the safety follow-up period and the investigator considers that there is a reasonable causal relationship between the SAE and the study drug, it should be reported to the sponsor according to the SAE reporting process.
 
[16] After the final tumor imaging assessment, the patients will be contacted by phone or in-person every 12 weeks (<math>\pm 7</math> days) to collect information on their survival status and subsequent anti-tumor treatment.
 |

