## 5. Study Population

### 5.1. Inclusion Criteria

- (1) Voluntarily participate in this study and sign the informed consent form;
- (2) Aged 18 ~ 75 years old (inclusive), male or female;
- (3) Patients with histologically or cytologically confirmed unresectable locally advanced or metastatic NSCLC;
- (4) RET gene fusion, as demonstrated by the "Next-generation" sequencing(NGS) method in the central laboratory with College of American Pathologists(CAP) or Clinical Laboratory Improvement Amendments(CLIA) certification;
- (5) Progressive disease after at least one line of the standard of care (including patients with disease progression during or within 6 months of the end of adjuvant therapy);
- (6) At least one measurable lesion according to RECIST 1.1 (for lesions previously treated with radiation, the lesion can be included as a measurable lesion only if there is clear disease progression after radiotherapy);
- (7) Eastern Cooperative Oncology Group (ECOG) performance status (PS) score 0-1;
- (8) Adequate organ function, laboratory tests meeting the following criteria:
  - Neutrophil count (ANC)  $\geq 1.5 \times 10^9/L$  (no G-CSF for WBC-elevating therapy within 2 weeks prior to the laboratory test);
  - Platelet count (PLT)  $\geq 75 \times 10^9/L$  (no platelet transfusion or other drugs to promote platelet production within 2 weeks before the laboratory test);
  - Hemoglobin (Hb)  $\geq 90$  g/L(not receiving red blood cell transfusion or erythropoiesis-stimulating drugs within 2 weeks before the laboratory test);
  - Alanine aminotransferase (ALT) and aspartate aminotransferase (AST)  $\leq 3 \times$

upper limit of normal (ULN) ( $\leq 5.0 \times \text{ULN}$  for patients with liver metastases);

- Serum total bilirubin (TBIL)  $\leq 1.5 \times \text{ULN}$ ;
- Serum creatinine  $\leq 1.5 \times \text{ULN}$ ;
- Albumin  $\geq 30 \text{ g/L}$ ;

- (9) Male and female patients of childbearing age must agree to take effective contraceptive measures during treatment and for 6 months after.

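### For female patients the stated pregnancy-reporting duty ends about 28 days after the last dose, but the protocol requires contraception for 6 months, and Section 8.3.9 is not consistent on the period

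*Protocol*

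**What the plan says.** - **Contraception.** Inclusion criterion 9 in Section 5.1 reads "Male and female patients of childbearing age must agree to take effective contraceptive measures during treatment and for 6 months after". The synopsis (Section 1.1) fixes the starting point of the 6 months: patients must "agree to take effective contraceptive measures during treatment and within 6 months after the last dose of treatment".
- **Pregnancy reporting, female patients.** The first sentence of Section 8.3.9 obliges the investigator to report pregnancies in female patients "during the administration of the drug and throughout the safety follow-up period to the sponsor".
- **End of that period.** Section 8.3.7 has adverse events collected "from the signing of the informed consent form to the end of the safety follow-up period" and puts that end at 28 ± 3 days after the last dose. The schedule in Section 1.2 places the safety visit at "Day 28 after the last dose", with the same 3-day window.
- **Partners of male patients.** Section 8.3.9 asks for information on the course and outcome of the pregnancy, subject to the partner's consent. It gives no end date.
- **Speed of reporting.** Section 8.3.9 requires a form within 24 hours of a confirmed pregnancy in a patient or a partner, again without an end date.
- **Other chances to detect a pregnancy.** The last scheduled test is at the end-of-treatment visit, within 14 days of the last dose (Sections 1.2 and 8.2). After the final tumor imaging, "the patients will be contacted by phone or in-person every 12 weeks" (Section 1.2, note 16), but only to record survival and further cancer treatment.

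**The concern.** By asking for contraception for 6 months after treatment, the protocol marks those months as a time in which conception should be avoided. The reporting rule for female patients stops after roughly the first of them. A site that follows the first sentence of Section 8.3.9 has no stated duty to report a conception in, say, month 3. It also has no scheduled test or question that would bring such a conception to light.

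What is at stake is patient safety information. The sponsor would learn of pregnancies in most of its own post-treatment precaution period only by chance. The protocol's background gives some reason for interest: Section 2.2.3 lists the female reproductive system among the target organs of toxicity in the 28-day rat study.

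**Working it through.** The plan states no figure of its own on this point, so the check is day arithmetic on its stated periods, followed by a reading of what else could cover the gap.

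**Inputs**
- Safety follow-up after the last dose, *s*: 28 days, range 25 to 31 (Sections 8.3.7 and 1.2).
- Contraception period after the last dose, *D*: 6 months (inclusion criterion 9). The protocol does not convert this to days. I assume 183 days and also try 168 and 180.

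**Formula.** Uncovered days = *D* − *s*. Uncovered share = 1 − *s*/*D*.

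| *D* (days) | *s* = 25 | *s* = 28 | *s* = 31 |
|---|---|---|---|
| 168 | 143 (85.1%) | 140 (83.3%) | 137 (81.5%) |
| 180 | 155 (86.1%) | 152 (84.4%) | 149 (82.8%) |
| 183 | 158 (86.3%) | 155 (84.7%) | 152 (83.1%) |

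The central case is 1 − 28/183 = 0.847, that is, 155 uncovered days. The full range is 81.5% to 86.3%.

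**If time on treatment is counted.** With *T* days of treatment, all covered by the reporting rule, the uncovered share of the whole contraception period is 155/(*T* + 183):
- *T* = 28: 155/211 = 73.5%
- *T* = 127: 155/310 = 50%
- *T* = 168: 155/351 = 44%
- *T* = 336: 155/519 = 30%

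So the figure of about 85% belongs to the post-treatment period only.

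**Does anything else close the gap for female patients?**
- *Tests:* the last one is at the end-of-treatment visit.
- *Adverse events:* Section 8.3.7 ends active collection with the safety follow-up. After that, only serious events with a reasonable causal link to the drug are to be reported. Congenital anomaly is on the list of seriousness criteria in Section 8.3.1.4; pregnancy is not.
- *Later contacts:* note 16 of the schedule includes no pregnancy question. These contacts also start only after the final tumor imaging. A patient who stops treatment without progression stays on the imaging schedule (Sections 7.1 and 8.1) and may have imaging visits but no survival contact during the 6 months.
- *The 24-hour sentence:* it has no end date, but it sets how fast a known pregnancy is reported. It creates no occasion on which one would be found.

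**Consistency within Section 8.3.9.** The first sentence limits the period for female patients. The partner sentence and the 24-hour sentence have no limit. The counselling sentence, which addresses patients of both sexes, refers again to the safety follow-up period. A site cannot tell from this which period applies to whom.

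**The case against.** The best case on the other side has five parts.

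1. *The limit does not apply to every pregnancy.* A reader might infer that all reporting stops at day 28. The text does not support that. The limit is written for female patients, and a partner rule without an end date is, taken literally, wider than 6 months. This stands, and the 81.5% to 86.3% does not apply to partners.
2. *The 24-hour sentence may already cover a late pregnancy.* A site could read it that way for a month-3 pregnancy it happens to hear of. This stands in part: the section is ambiguous rather than plainly exclusionary. Even on this reading nobody is told to ask, and the first sentence still says otherwise.
3. *Late congenital anomalies are not lost.* A reader might infer that they would be. An anomaly that is reported to the site and judged related to the drug remains reportable as a late serious event. This stands, though it depends on the site hearing of it and on the causality judgement, and it does not cover the pregnancy itself.
4. *No planned endpoint is damaged.* One might infer that the secondary safety objective is compromised. The safety endpoint in Section 3 is restricted to the treatment period, so a conception months later lies outside it. The protocol also gives no human half-life from which fetal exposure at that time could be shown. This stands.
5. *A contraception undertaking and a reporting period are different instruments.* Nothing in the protocol says they must be equal. This is true, and it is why the mismatch is a design weakness rather than a formal contradiction. The protocol gives no reason for ending reporting so much earlier.

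**Conclusion.** The concern holds for female patients in the period after treatment. About 85% of that period (81.5% to 86.3% over the ranges tried) has no stated reporting duty and no scheduled pregnancy question. Section 8.3.9 is also inconsistent about the period, because two of its sentences have no end date.

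The size rests on the assumed conversion of 6 months to 168 to 183 days and on the 25 to 31 day window for the safety visit. It should not be read as the share of the whole contraception period: once treatment time is counted, the gap is more than half only if treatment lasts less than about 127 days. The protocol gives no pregnancy rate, so no number of missed pregnancies can be estimated.

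This is a worthwhile, inexpensive safety improvement. It has no bearing on the response-rate analysis, the sample size or the treatment-period safety endpoint.

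**What to change.** Reconcile Section 8.3.9 with inclusion criterion 9. State one pregnancy-reporting period, for female patients and for partners of male patients, that runs to the end of whatever contraception period the protocol keeps. Make the first sentence, the partner sentence, the counselling sentence and the 24-hour sentence all refer to it. How long contraception should last is for the sponsor to decide; the point here is only that the two periods should agree.

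Add a pregnancy question at whichever contact is already scheduled in that period: the tumor-imaging visit for patients still being imaged, the 12-weekly survival contact for the others. Relying on the survival contacts alone would miss patients who stopped treatment without progression. Note 16 of the schedule should list the question.

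The cost is a short amendment, one extra question at existing contacts and a few more pregnancy forms. No visit is added and no analysis changes.
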